## Background

Globally, cancers of oral cavity, breast and cervix account for approximately 15% of all cancer incidence. In India, these cancers account for one-third of all cancers and cause nearly 0.25 million deaths every year in the country [1]. The latest study that evaluated the cancer trends across the available 28 population-based cancer registries and 58 hospital-based cancer registries in India showed an increasing trend in cancer incidence across all sites in both sexes during 2012–2016. India’s first population-based rural cancer registry in Barshi, Maharashtra, also reported age-adjusted incidence rates between 50.6 per 100,000 and 61 per 100,000 among men and women in the rural population [2]. Cancer has a catastrophic impact on the rural communities in India, the majority of whom are socioeconomically disadvantaged, with one in ten living below the national poverty line [3]. The cost of treating cancer in rural India is among the highest for any disease due to the advanced stage of presentation [4]. Treatment for advanced and metastatic cancer is significantly more expensive than early stage. Treatment is primarily financed through out-of-pocket expenses, including borrowing, selling assets and financial assistance from friends and relatives [5]. Overall, 60% of households seeking care in the private sector experience catastrophic expenses. Fatality rates are also significantly higher for cancers in rural populations than in urban [6]. Access to cancer early detection and subsequent care is limited in rural India, due to geographical, infrastructural and financial barriers. While 70% of cancer patients live in rural areas, 95% of cancer care facilities are concentrated in urban centres, forcing patients to travel long distances for diagnosis and treatment. In addition, the rural population in India faces several sociocultural barriers such as stigma and fear of cancer. Coupled with the financial burden and limited health infrastructure in rural health centres, these urban–rural disparities have contributed to increased treatment dropout rates among the rural population [7].

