### Sampling methodology and sample size estimation

WP2 involves a population survey. A multistage cluster sampling design will be employed to select participants for the surveys. Blocks will serve as the primary sampling units and households as the secondary sampling units. Based on an expected 50% prevalence of knowledge and understanding about common cancer symptoms and assuming a 10% precision, 95% confidence level and 20% nonresponse rate, a total sample size of 480 is estimated for each state [36]. This sample size will be proportionally divided among randomly selected blocks. Subsequently, the number of households from each block will be proportionately distributed using systematic sampling from a list of households. One respondent from each household, alternating male and female, will be chosen to get equal male and female participants. The number of participants required for the hospital-based survey in WP2 has been empirically decided at 100 patients with breast, cervical and oral cancer from each study site. It is estimated that a minimum of six FGDs per state will be conducted or more until saturation is achieved.

For WP3, the services will be broadly categorised into primary, secondary and tertiary healthcare settings. The number of facilities to be sampled will be calculated using the standard formula for a proportion using an expected percentage of health facilities offering a given service as the outcome. An expected proportion of 90% of service availability will be used, with 95% confidence within an error margin of 20%, assuming a nonresponse rate of 10% of the selected facilities. If the total number of a particular type of facility for each stratum is small (<4) in the district, all facilities may be included.

For WP4, the sample size will depend on the interventions and strategies selected to be piloted and evaluated.

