### Data analysis

For qualitative methods, data will be analysed through the content analysis technique. This technique consists of the following three stages; pre-analysis, coding and categorisation and inference and interpretation.

The pre-analysis consists of organising the data in the district within a framework and deciding the level of analysis (word, phrase and sentence). Next, the interviews will be fully transcribed and translated to create the body of research. The coding will be done using the codification tools, and codes will be grouped into themes and categories. The team will discuss themes and types to check their reliability, and a conceptual model will be developed. Finally, we will proceed with the inference and interpretation of the results. The outcomes will be summarised to prepare a detailed report, which will help us perform the strength, weakness, opportunity and threat (SWOT) analysis and draft the capacity development response.

For quantitative methods, data cleaning and consistency checks will be performed. The facility survey data will be analysed using descriptive statistics to describe the overall capacity of health systems. For each facility and dimension, a summary score will be obtained and presented as percentages.

These reports will be compiled together for critical analysis of the strengths, weaknesses, opportunities for improvements and possible threats, particularly in augmenting the services to introduce or scale up new interventions (e.g., the introduction of HPV test or a navigation system). For the intervention phase, structural and process indicators analysed quantitatively to be used to assess the interventions objectively.

For the ISAT, the information will be synthesized (based on the data collected from the interventions, other WPs as well as from local practice-based information). The responses will generate scores that will be put in an SWOT matrix, which will allow us to understand the scalability of different interventions. The sustainability and scalability of interventions will be listed for each study site as well as visual representation of scores across each domain.

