The National Programme for Prevention and Control of Cardiovascular Disease, Diabetes, Cancer and Stroke (NPCDCS) and the Ayushman Bharat program are two examples of India’s health system reforms that are intended to increase access to healthcare, notably for noncommunicable diseases such as cancer. While NPCDCS encourages cancer prevention and early detection, Ayushman Bharat’s Health and Wellness Centers concentrate on primary healthcare and cancer screening. Nevertheless, both programs encounter obstacles such as inadequate rural healthcare facilities, limited workforce and low awareness. By creating context-specific strategies to increase access to cancer screening and subsequent care in rural India, this project seeks to close these gaps and strengthen the implementation of these national initiatives [39, 40].

Several large-scale initiatives from low- and middle-income countries (LMICs) have shed light on effective implementation strategies for cancer screening and subsequent care. Recently, the WHO has laid out a strategic agenda for the effective scale-up of HPV-based screening across LMICs, including India [41]. Furthermore, recent studies have documented that successful scale-up of cancer early detection services across LMICs requires consideration of evidence-based resource stratified intervention that would fit local health infrastructure [42, 43]. The WHO Cervical Cancer Elimination Initiative also highlights the importance of establishing comprehensive health systems and community engagement to raise awareness and improve screening uptake [44]. Furthermore, strengthening partnerships among healthcare providers, local organizations and community members can enhance the effectiveness of cervical cancer prevention and treatment efforts. WHO’s recent navigation guide highlights the significance of guiding patients through early detection and treatment processes, emphasizing the need for research to identify local barriers. Identifying, implementing and integrating these elements will enhance the study’s relevance and increase its potential impact on patient outcomes and healthcare accessibility in resource-constrained settings.

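### The WP3 facility survey is sized on an unsupported 90% availability with a 20% margin: this implies about nine facilities per estimate, an interval past 100%, and a margin missed at intermediate availability

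*Protocol article*

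**What the plan says.** The section on sampling methodology and sample size estimation fixes the inputs for WP3. The method comes first: "The number of facilities to be sampled will be calculated using the standard formula for a proportion". The quantity to which that method is applied is then described: "using an expected percentage of health facilities offering a given service as the outcome". The planning values follow: "An expected proportion of 90% of service availability will be used, with 95% confidence within an error margin of 20" per cent. An allowance is added for facilities that do not take part: "assuming a nonresponse rate of 10% of the selected facilities". Very small strata are covered by a separate rule: "If the total number of a particular type of facility for each stratum is small (<4) in the district, all facilities may be included".

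The article gives no resulting number of facilities. It does not name the service, give a basis for the 90%, say whether the 20% is absolute or relative, or say whether the size applies per facility type, district or state.

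Under Data analysis, "The facility survey data will be analysed using descriptive statistics to describe the overall capacity of health systems", with a summary score per facility and dimension shown as percentages.

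**The concern.** A 20-point margin around 90% passes 100%, which shows that the normal formula is being used outside its range. An expected value near 0 or 1 also makes the formula return a small sample, so the promised precision depends on the 90% being right. The article gives some reason to doubt it. The Background says "Access to cancer early detection and subsequent care is limited in rural India". The Discussion says of the two national programmes that "both programs encounter obstacles such as inadequate rural healthcare facilities, limited workforce and low awareness". The Rajasthan setting is described as having had no screening activity.

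The WP3 percentages feed the SWOT analysis and the capacity development response, and they are part of what stakeholders see when interventions are chosen in WP4. A reader who takes the 20% margin at face value will treat these percentages as more precise than they are.

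**Working it through.** **Inputs.** From the sampling section: p = 0.90, 95% confidence (z = 1.96), margin 20%, nonresponse 10%. No WP3 sample size is printed, so there is no figure to reproduce; the sizes below are derived. They apply per estimate and, until step 5, ignore finite-population correction.

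**1. Implied size**, n = z²p(1−p)/d².
- Absolute margin, d = 0.20: 3.8416 × 0.09 / 0.04 = 8.64, so 9 responding; 9/0.9 = 10 selected. Implied interval 70% to 110%.
- Relative margin, d = 0.2 × 0.9 = 0.18: 3.8416 × 0.09 / 0.0324 = 10.67, so 11 responding; 11/0.9 = 12.2, so 13 selected. Implied interval 72% to 108%.

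The ambiguity is real. The WP2 figure of 480 in the same section follows from its stated inputs, with no further multiplier, only if its 10% precision is relative to 50% (d = 0.05): 3.8416 × 0.25 / 0.0025 = 384.16, and 384.16/0.8 = 480.2. With d = 0.10 the result is 96.04/0.8 = 120.

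**2. Is the approximation usable?** At n = 9 and p = 0.9, np(1−p) = 0.81, and only 0.9 facilities are expected to lack the service. The chance that all nine offer it is 0.9⁹ = 0.39.

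**3. Valid 95% intervals with nine facilities.**

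| Offering service | Wilson | Exact (Clopper–Pearson) | Lower arm, points |
|---|---|---|---|
| 9/9 | 70.1–100% | 66.4–100% | 30–34 |
| 8/9 | 56.5–98.0% | 51.8–99.7% | 32–37 |
| 7/9 | 45.3–93.7% | 40.0–97.2% | 32–38 |
| 6/9 | 35.4–87.9% | 29.9–92.5% | 31–37 |
| 5/9 | 26.7–81.1% | 21.2–86.3% | 29–34 |

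Results of 0 to 4 mirror these. No result among nine gives an interval whose longer arm is 20 points or less. Under the relative reading, 10 of 11 gives Wilson 62.3–98.4% and exact 58.7–99.8%, a lower arm of 29 to 32 points.

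**4. Dependence on the 90%** (absolute margin, nine facilities; half-width = 1.96√(p(1−p)/9); within-20 probability from the binomial distribution).

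| True availability | Half-width, points | Chance estimate is within 20 points | Facilities the formula asks for |
|---|---|---|---|
| 0.9 or 0.1 | 20 | 94.7% | 9 |
| 0.7 or 0.3 | 30 | 86.1% | 21 |
| 0.5 | 33 | 82.0% | 25 |

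The 82% is P(3 ≤ X ≤ 6) = (84 + 126 + 126 + 84)/512 = 420/512. The 25 is 3.8416 × 0.25/0.04 = 24.01, rounded up; 25/0.9 = 27.8, so 28 selected.

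**5. Finite strata.** Stratum sizes are not given, so these are assumed.
- If nine facilities are visited in a stratum of N, the half-width at 50% is 32.7 × √((N−9)/(N−1)): 24.9 points for N = 20 and 29.9 for N = 50. It drops below 20 points once N is 13 or less (32.7 × √(4/12) = 18.9).
- If the correction is used instead to reduce the visits so that the margin is just 20 points at 90%, then before rounding the half-width at 50% is 20 × √(0.25/0.09) = 33 points whatever N is.

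**The case against.** The strongest reply is that no printed figure is wrong and that the plan works under its own assumption: at a true 90%, nine facilities put the estimate within 20 points 94.7% of the time. That stands. The failure concerns valid interval width and availability away from the extremes. It also stands that the article proposes no interval method for these data, so poor coverage of a normal-theory interval cannot be charged to it. Nor is any test at stake: WP3 is descriptive, is checked with stakeholders and is triangulated with WP1 and WP2. That limits the consequence but does not make the stated margin correct.

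Three stronger readings are tempting, and the documents do not support them.

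- *The 90% contradicts the article.* The service is unnamed, and limited access or inadequate facilities are not a share of facilities offering a service. Kerala and Tamil Nadu are described as better or well organised. Only Rajasthan conflicts directly, and only if the service is cancer screening. Near-absent services (10%) would give the same sample size as 90%. This is tension, not contradiction.
- *The rule for fewer than four facilities clashes with a formula asking for ten.* With finite-population correction, n = 8.64/(1 + 7.64/N) gives 2.4 for N = 3 (all three), 2.97 for N = 4 (three) and 4.7 for N = 9 (five). Before nonresponse, the threshold is about where a census becomes necessary. The article does not mention the correction, but it may be in the full protocol.
- *An overall capacity figure will overstate rural capacity because levels of care are pooled unweighted.* The article gives no facility counts and never says the levels are pooled without weights.

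**Conclusion.** The point holds in a limited form. The stated inputs imply about 9 responding facilities per estimate (11 if the margin is relative) and an interval above 100% on either reading. At 8 of 9, a valid interval has a lower arm of 32 to 37 points. At 50% availability, the half-width is about 33 points, the estimate is within 20 points 82% of the time, and 25 facilities would be needed for ±20. The 20-point margin therefore describes the point estimate at one assumed availability (and its mirror image, 10%), not the design across the availabilities the survey may meet. The 90% is unsupported and is among the values that keep the sample small.

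This rests on simple random sampling within each stratum, on the derived size being the one used, and on strata large enough that finite-population correction does not remove most of the error. In small strata visited nearly in full, the shortfall shrinks or disappears.

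**What to change.** Keep the planned number of visits. Replace the single statement of 90% with a 20% margin by the precision expected over a range of availability, for example 0.2 to 0.9 with 0.5 as the conservative case. Compute it with Wilson or exact intervals and finite-population correction for each stratum. Say whether the margin is absolute or relative, name the service, and state the unit to which the size applies.

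The cost is wording plus a facility count per stratum, which the sampling frame needs anyway. The drawback is that the stated margin becomes wider: around 30 points or more for nine facilities in a large stratum. If a 20-point margin is really needed whatever the availability, the alternative is about 25 responding facilities (28 selected) per estimate before finite-population correction, which means more visits.

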### Data management

Trained data entry personnel will enter the data into REDCap electronic data capture tools (https://projectredcap.org/) with regular quality checks by each site PI. For surveys conducted electronically, the data will be automatically recorded in a structured format within REDCap. After the data entry process, a thorough data cleaning procedure will be conducted to identify and correct errors, inconsistencies and missing values. Data cleaning will be achieved with a range of techniques, such as validating responses against predefined criteria, checking for outliers and resolving any discrepancies or inconsistencies. Data cleaning procedures will be documented to ensure transparency and reproducibility of the data management process. Regular backups of the data will be performed to prevent data loss and ensure data integrity. For qualitative methods, the informants’ consent, the interviews will be audio recorded, transcribed and reviewed by a researcher to ensure validity. The data will be anonymized, and identification codes will be used for confidentiality. Identifiable data will be housed under the custodianship of local PIs. All other data for purposes of health systems and economic analysis will be under the custodianship of Co-PIs in compliance with local data management policy(s), data security and sharing policy. Data managed using REDCap will be hosted and stored at IARC and will be shared with KCL through a data transfer agreement. Anonymised data will be archived in IARC to allow retrieval for any scientific or regulatory external audits.

### Data analysis

For qualitative methods, data will be analysed through the content analysis technique. This technique consists of the following three stages; pre-analysis, coding and categorisation and inference and interpretation.

The pre-analysis consists of organising the data in the district within a framework and deciding the level of analysis (word, phrase and sentence). Next, the interviews will be fully transcribed and translated to create the body of research. The coding will be done using the codification tools, and codes will be grouped into themes and categories. The team will discuss themes and types to check their reliability, and a conceptual model will be developed. Finally, we will proceed with the inference and interpretation of the results. The outcomes will be summarised to prepare a detailed report, which will help us perform the strength, weakness, opportunity and threat (SWOT) analysis and draft the capacity development response.

For quantitative methods, data cleaning and consistency checks will be performed. The facility survey data will be analysed using descriptive statistics to describe the overall capacity of health systems. For each facility and dimension, a summary score will be obtained and presented as percentages.

These reports will be compiled together for critical analysis of the strengths, weaknesses, opportunities for improvements and possible threats, particularly in augmenting the services to introduce or scale up new interventions (e.g., the introduction of HPV test or a navigation system). For the intervention phase, structural and process indicators analysed quantitatively to be used to assess the interventions objectively.

For the ISAT, the information will be synthesized (based on the data collected from the interventions, other WPs as well as from local practice-based information). The responses will generate scores that will be put in an SWOT matrix, which will allow us to understand the scalability of different interventions. The sustainability and scalability of interventions will be listed for each study site as well as visual representation of scores across each domain.

### Study monitoring

We will use a set of comprehensive input measures, milestones and outcome measures and develop and implement a dedicated information system for each WP. Site visits by the study monitor from the IARC will be arranged at study initiation and once every 6 months. Good clinical practices and Good Laboratory Practices will be implemented. Standardised questionnaires and standard operating procedures (SOP) will be developed for each of the procedures to collect data and adherence to it will be monitored regularly. Data entry and management SOPs will also be used.

### Ethical consideration

The protocol was registered prospectively on 27/9/2022 with the Clinical Trial Registry India (CTRI number CTRI/2022/09/045927). We have obtained ethical approval from the IARC Ethical Committee (IARC IEC 22-05) and will report progress for further approvals on interventions in a timely manner.

Each study site has also obtained site-specific ethical approval (HMSC 2022-17547). We will obtain written informed consent from all respondents before we begin data collection. Participation in the study is entirely voluntary. Before the intervention phase, we will obtain a separate ethical approval from each site for the final set of interventions and implementation strategies decided.

## Discussion

This study will investigate the potential to implement evidence-based interventions tailored to the specific context of three Indian states, each with distinct organisation of health system and health outcomes. Recognizing the importance of stakeholder engagement and local capacity, we aim to co-develop intervention elements and implementation strategies that are ‘best fit’ from the perspectives of the organization and populations/patients identified.

Specifically, this research will explore the feasibility of implementing effective early detection and management strategies for three distinct states with varied levels of cancer care organization maturity, providing an opportunity to assess the effectiveness of different approaches under various contexts. In Tamil Nadu, the Tamil Nadu Health Systems Project was an initiative of the government, in partnership with the World Bank, to create a health system that is highly accessible, equitable and effective. This initiative included a cervical cancer screening and treatment pilot program with good coverage. However, the programme resulted in relatively low VIA positivity, high loss to follow-up and low levels of treatment provision, likely due to gaps within the health system [37]. The pre-intervention phase of the current study will dive deep into these health system gaps and explore ways to facilitate patient follow-up and a quality-assured programme. In Kerala, the state government is currently establishing the Kerala Cancer Care Grid as part of the Kerala Cancer Control Strategy 2018–30 to ensure equitable access to affordable cancer detection and treatment services [38]. The findings of this study will support and complement this ongoing effort by the state government, recognising that any strategy proposed for the scale-up must be owned to be sustained.

The proposed effectiveness–implementation hybrid design is valuable in implementation research, enabling simultaneous evaluation of effectiveness of the proposed intervention though primarily focusing on feasibility, acceptability, adoption and maintenance of its implementation in real-world settings. This design is a pragmatic way of conducting implementation research considering the constraints policymakers and programme managers face in relation to evidence informed decision-making. It may help alleviate any public relations and political concerns that the local stakeholders might have when conducting public policy experiments by promoting collaboration, respecting local contexts, providing actionable insights and promoting sustainability.

The expected outcome of this study is to develop and evaluate a context-appropriate, evidence-based strategy that improves access to early detection and care of oral, breast and cervical cancers in rural India. The findings will provide valuable insights into how tailored interventions can reduce delays in diagnosis, improve treatment adherence and enhance overall cancer care in rural settings. If successful, these strategies can be adapted and scaled to other states across India, where similar barriers to cancer care exist. The findings from our study can serve as a model for other states with comparable challenges, enabling policymakers and health authorities to design localized, scalable cancer care interventions. This could ultimately contribute to nationwide improvements in cancer care access and outcomes, particularly in underserved rural areas, helping to bridge the urban–rural gap in healthcare delivery.

The National Programme for Prevention and Control of Cardiovascular Disease, Diabetes, Cancer and Stroke (NPCDCS) and the Ayushman Bharat program are two examples of India’s health system reforms that are intended to increase access to healthcare, notably for noncommunicable diseases such as cancer. While NPCDCS encourages cancer prevention and early detection, Ayushman Bharat’s Health and Wellness Centers concentrate on primary healthcare and cancer screening. Nevertheless, both programs encounter obstacles such as inadequate rural healthcare facilities, limited workforce and low awareness. By creating context-specific strategies to increase access to cancer screening and subsequent care in rural India, this project seeks to close these gaps and strengthen the implementation of these national initiatives [39, 40].

Several large-scale initiatives from low- and middle-income countries (LMICs) have shed light on effective implementation strategies for cancer screening and subsequent care. Recently, the WHO has laid out a strategic agenda for the effective scale-up of HPV-based screening across LMICs, including India [41]. Furthermore, recent studies have documented that successful scale-up of cancer early detection services across LMICs requires consideration of evidence-based resource stratified intervention that would fit local health infrastructure [42, 43]. The WHO Cervical Cancer Elimination Initiative also highlights the importance of establishing comprehensive health systems and community engagement to raise awareness and improve screening uptake [44]. Furthermore, strengthening partnerships among healthcare providers, local organizations and community members can enhance the effectiveness of cervical cancer prevention and treatment efforts. WHO’s recent navigation guide highlights the significance of guiding patients through early detection and treatment processes, emphasizing the need for research to identify local barriers. Identifying, implementing and integrating these elements will enhance the study’s relevance and increase its potential impact on patient outcomes and healthcare accessibility in resource-constrained settings.

Most evidence-based interventions for cancer early detection are designed, implemented and evaluated in high-income countries. These interventions and strategies are not readily transferable to LMICs. Implementation research such as this can contribute significantly to the development of cancer policies and operational frameworks by identifying context-specific challenges and developing effective strategies to overcome these challenges. In LMICs, this is particularly important, as these countries operate with limited resources and healthcare infrastructure, which can pose significant challenges to implementing effective cancer early detection programmes. With the sharing of this protocol, we aim to contribute to the evidence based on implementation science-based research related to cancer early detection, diagnosis and treatment beyond India to other similar LMIC settings.

